#### 4.1.5 Sample Size Estimation

Available trial data from each subject who received at least one dose of study medication will be used in the primary safety analysis. Using PASS2000 (NCSS Software), a total of 45 subjects (15 per group) will be enrolled into the study to ensure that approximately 39 subjects (13 per group) complete the study under the following sample size assumptions:

- A parallel group design is employed, with equal randomization between the groups.
- The primary endpoint is relative insulin response over time.
- The comparison is made using a Type I error rate of 0.05.
- The comparison is assessed using a Type II error rate of, at most, 0.2 which provides a minimum power to detect the specified difference 80%.
- An F-test from a repeated measures ANOVA model including a fixed treatment effect and a random effect for time is used to test the null hypothesis of no treatment difference.
- The baseline value for the placebo group is 0.23. A 15% difference is expected in each of the treatment groups. A constant standard deviation of 0.20 is expected.
- The relative insulin response is calculated at baseline, week 1, week 4, week 8, and week 12.

Similar calculations suggest that a sample size of 13 subjects per group will be sufficient to detect a 5% change from baseline in HbA1c for each treatment group (including placebo) at week 12 under the following sample size assumptions:

- Each comparison is made using a Type I error rate of 0.05.

- Each comparison is assessed using a Type II error rate of, at most, 0.2 which provides a minimum power to detect the specified difference 80%.
- An effect size of 1 is expected.
- A paired t-test is used to test the null hypothesis of no treatment difference.

#### 4.1.6 Randomization

Within each center, the investigator or his/her designate will determine whether the patient has met all inclusion/exclusion criteria and is eligible for entry into the study. Patients meeting all inclusion/exclusion criteria and providing written informed consent will be randomized at Visit 3, after completion of the lead-in period, which begins at Visit 2.

To maintain balance of treatment assignments among insulin use groups (insulin use, no insulin use), eligible patients will be randomly allocated in balanced blocks to either the TH9507 1 mg, TH9507 2 mg, or placebo treatment groups according to computer generated randomization codes for each insulin use group maintained by an external randomization center. To ensure that at least 3 subjects either in the insulin use or non-insulin use group complete the study for each treatment arm, enrollment for the larger group may be halted after 33 patients have been randomized for that group. Enrollment would continue for the smaller group until approximately a total of 12 subjects have been randomized for that group.

Study drug supplies will be assigned sequentially by the investigator, or his/her designate, within each center, using the subject randomization number assigned by the randomization center.

Subjects may not be randomized into the study more than once, and once a subject randomization number has been assigned, it may not be reused.

Assignment of the randomization number to a subject defines enrollment into the study.

#### 4.1.7 Blinding

The study is designed to be double-blind. Active drug and placebo will be provided as lyophilized powder in vials of identical appearance and supplied in blister cards covering a one month period at each monthly visit. Each dosage regimen is supplied as two vials according to the following 'double-dummy' specification:

- 1 mg TH9507 as one vial of 1.1 mg active drug and one vial of placebo
- 2 mg TH9507 as two vials of 1.1 mg of active drug
- placebo as two vials of placebo

The randomization code for each subject is supplied to the participating center in sealed envelopes that will only be opened in case of emergency. The study blind will be broken and treatment assignment will be made available for data analysis after the database has been locked and protocol violations have been determined.

#### 4.1.8 Data Transformations

It is intended that the analysis of the primary endpoint will be based on relative insulin response. However, appropriate transformations will be performed as required to satisfy assumptions required to perform statistical analyses. Descriptive statistics will be provided for these transformed variables.

#### 4.1.9 Strategy for Statistical Analysis

The safety population is defined as all subjects who were randomized and received at least one dose of study medication (1 mg TH9507, 2 mg TH9507, or placebo) during the course of the trial. This is the primary population for analysis.

The change from baseline values for biochemical laboratory parameters (secondary endpoints) will be analyzed using analysis of variance techniques (ANOVA) which focus on the between (different regimens) and within (same regimen) comparisons of these measurements over time, with center and insulin use group included as fixed effects. Analyses may be conducted as repeated measures analyses or individual analyses of specific study visits.

Glucose values will be obtained at home four times per day using a standardized glucose meter. Subjects will record glucose values in their diary. Glucose values, downloaded electronically from the glucose meters, will be used for statistical analysis.

The assessment of safety will be based mainly on the frequency of adverse events and on the number of laboratory values that fall outside of predetermined ranges. Other safety data (e.g. vital signs, special tests) will be considered as appropriate.

Adverse events will be summarized by presenting, for each treatment group, the number and percentage of subjects having any adverse event, having an adverse event in each body system and having each individual adverse event. Any other information collected (e.g. severity or relatedness to study medication) will be used to categorize the adverse event data as appropriate.

Laboratory data will be summarized by presenting shift tables using extended normal ranges (baseline to most extreme post-baseline value) by presenting summary statistics of raw data and change from baseline values (means, medians, standard deviations, ranges) and by flagging of notable values in data listings.

#### 4.1.10 Interim Analyses

No formal interim efficacy analyses are planned.

#### 4.1.11 Dropouts, Protocol Deviations and Exclusions

Subjects may end their participation in the study at any time for any reason(s). These subjects will be encouraged to provide a termination assessment at this time.

Patients screened for enrollment into the study but found to be ineligible will be excluded from entry. A log of exclusions, along with the reasons for exclusion, will be maintained. Ideally, this information will consist of the inclusion/exclusion case record form criteria for each excluded subject. The extent of the information collected will depend on the ethical guidelines within each center. This information can then be used to characterize the population being screened but excluded from the trial. Should enrollment problems be encountered during the trial, this information may indicate the primary reason(s).

All protocol deviations will be documented and categorized in the final clinical trial report according to standard classifications.

## STANDARD PROTOCOL DEVIATION CATEGORIES

1. Entrance Criteria Not Met
2. Patient Received Incorrect Trial Medication
3. Concomitant Medication Violation
4. Missed Visit, Evaluation or Test
  - Missed Visit
  - Missed Evaluation
  - Missed Test
  - Missing Required Source Documentation
  - Missed Daily Record
  - Incomplete Daily Record
5. Incorrect Timing of Visit, Evaluation or Test
  - Incorrect Timing of Visit
  - Incorrect Timing of Evaluation
  - Incorrect Timing of Test
6. Informed Consent Signed After Entry of Subject into Trial
7. Trial Medication Non-Compliance
8. Incorrect Patient Number Assignment
  - Patient Number Assigned Out-Of-Order
9. Other

Examples of evaluations include physical examination and laboratory tests.

### 4.1.12 Handling of Missing Data

As the primary objective of this study is to assess the safety of the two doses of TH9507, no special handling of missing data are planned.

A secondary analysis for the primary endpoint will be assessed using the method of last-observation-carried-forward (LOCF) will be used to impute the data required for the assessment of the primary objective.

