### 3.3.3 Interruption or Discontinuation of Treatment

Before interrupting or discontinuing study drug, the investigator must contact the sponsor or designee (except in the case of an emergency) to discuss the proposed reason. It will be documented whether or not each subject completed the clinical study. If any subject's study treatment or observations were discontinued, the reason will be recorded. Reasons that a subject may discontinue participation in this clinical study may be one or more of the following:

- Adverse event(s)
- Abnormal laboratory value(s)
  - Hemoglobin: decrease below 9.0 gm/dL
  - AST:  $\geq 3 \times$  ULN (upper limit of normal)
  - ALT:  $\geq 3 \times$  ULN
  - LDH:  $\geq 3 \times$  ULN
  - Alkaline Phosphatase:  $\geq 2 \times$  ULN
  - Triglyceride:  $\geq 1000$  mg/L
  - Creatinine:  $>2$  mg/dL
- **Any fasting glucose  $>300$  mg/dL and/or any HbA1c value of  $>12\%$  in spite of ad lib adjustments to oral hypoglycemic agents and/or insulin dosage.**
- Subject withdrew consent
- Lack of compliance to protocol requirements and/or procedures
- Lost to follow-up

- Administrative deviations which preclude satisfactory completion of protocol assessments

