- Instruct the subject to withhold oral sulfonylurea, insulin, and other insulin secretagogues but he/she may take oral non-sulfonylurea hypoglycemic medication (if oral insulin sensitizer) in the morning of Visit 6 and Visit 7.
- Instruct the subject to collect urine the day before the scheduled visit (starting at 6AM) until the morning (6AM) of the clinic visit.
- Schedule Visit 6 to occur 25-31 days following Visit 5, OR
- Schedule Visit 7 to occur 25-31 days following Visit 6.

VISIT 7: (Week 12  $\pm$  3 days)

- Assess adverse events.
- Review concomitant medications.

- Return all used and unused study drugs.
- Obtain body weight.
- Obtain vital signs (BP, RR, PR).
- Determine body mass index.
- Perform funduscopy with dilation by optometrist or ophthalmologist (may be performed within 5 days of date of Visit 7).
- Perform physical/neurological examinations (including examination for diabetic sensory neuropathy).
- Review/dispense diary.
- Download home glucose readings from previous 4 weeks.
- Dietician interview and assessment – caloric intake assessment, skin thickness (Harpender), waist/hip measurements, and body fat mass (Lange).
- Collect 24-hour urine for creatinine and nitrogen.
- Obtain blood (fasting) for laboratory tests – IGF-1, IGFBP-1, IGFBP-3, serum for TH9507 antibody, lipid profile, hematology, chemistry, HbA1C.
- Perform oral 3-hr GTT with 75Gm Glucose (Glucola).
- Obtain blood for insulin and glucose levels every 30 minutes during OGTT
- **Remind the subjects to call the clinic for any home blood glucose value that is >250 mg/dL.**
- **Investigator completes global assessment of diabetes control**
- Replenish boxes of strips and lancets, if necessary
- Subject receives NO STUDY DRUG AT THIS VISIT.
- Schedule Visit 8 (Post-treatment Visit) to occur 25-31 days following Visit 7.

VISIT 8: (Week 16 ± 3 days; Follow-up Visit; 16 weeks after randomization; 4 weeks post-treatment)

- Assess adverse events.
- Review concomitant medications
- Obtain body weight.
- Obtain vital signs (BP, RR, PR).
- Obtain blood for laboratory tests (hematology; blood chemistry; lipid profile)
- Collect urine for urinalysis.
- Schedule mammography (for females) and prostate examination/PSA (for males).
- Dietician interview and assessment – caloric intake assessment, skin thickness (Harpender) , body fat mass (Lange), and waist/hip measurements.
- Review diary.
- Download home glucose readings for the period since Visit 7.

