## 4. Statistical Methods

### 4.1 Statistical Methods to be Employed

#### 4.1.1 Study Objectives

This is a Phase II, placebo-controlled, comparative study. The primary objective is to evaluate the safety of two doses (1 mg and 2 mg by daily subcutaneous injection) of TH9507 relative to placebo administration, over a 12-week period in patients with stable, type 2 diabetes.

The primary endpoint is the change in relative insulin response following the oral ingestion of glucose over the 12-week treatment period. The relative insulin response is defined as the ratio of the incremental plasma insulin response above basal at 30 minutes to that of plasma glucose, divided by basal plasma insulin levels.

The secondary objectives are to evaluate the effects of 12 weeks of daily treatment with TH9507 on HbA1c, blood glucose measurements, **use of oral hypoglycemic agents and/or insulin and control of diabetes.**

The secondary endpoints include the change in HbA1c at Week 12 compared to baseline and changes in mean daily serum glucose concentrations compared to the 14 day lead-in period values, **changes in the number of dose adjustments per week for insulin and/or oral hypoglycemic agents compared to the 14 day lead-in period, and the number of subjects with a change in the control of diabetes.**

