### 4.1.13 Multiple Significance Testing

Unless otherwise specified, all p-values will be reported to four decimal places using two-sided tests of significance with no correction for multiplicity (multiple outcomes or multiple comparisons) having been employed. Statistical significance will be assessed at the conventional level of 0.05 in all cases unless otherwise stated, and thus any significant findings for parameters other than the primary endpoint must be interpreted accordingly.

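### The Week 12 HbA1c test and the diabetes-control count can lose the subjects whose control deteriorated most, and the plan has no handling for this

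*Protocol*

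**What the plan says.** - **Leaving the study.** Protocol section 3.3.3 lists reasons for which a subject may discontinue participation. One is a fasting glucose above 300 mg/dL and/or an HbA1c above 12% "in spite of ad lib adjustments to oral hypoglycemic agents and/or insulin dosage". The wording is permissive, and the reason for discontinuation is recorded.
- **HbA1c.** It is drawn at Weeks 0, 4, 8 and 12 (section 3.5.1). Section 4.1.4 fixes paired t-tests of Week 0 against Week 12 in each group. A repeated-measures model of change from baseline is optional there. Section 4.1.9 lets the laboratory ANOVA be run either as repeated measures or visit by visit.
- **Diabetes control.** Section 4.1.1 names as a secondary endpoint "the number of subjects with a change in the control of diabetes". The only listed source is at Visit 7 (Week 12) in section 3.5.1: "Investigator completes global assessment of diabetes control".
- **Early termination.** Section 4.1.11 says of subjects who leave: "These subjects will be encouraged to provide a termination assessment at this time". The text shown does not give the content of that assessment.
- **Missing data.** Section 4.1.12 reasons that, because the primary objective is safety, "no special handling of missing data are planned". It then adds LOCF as a secondary analysis of the primary endpoint, which is relative insulin response.

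**The concern.** The reason given for having no missing-data rule is that this is a safety study. Here that argument runs the wrong way, because the safety outcome is itself a listed cause of leaving. A subject who leaves for loss of glycaemic control before Week 12 has no Week 12 HbA1c to pair and reaches no Visit 7 rating. Nothing in the text provides for following that subject to Week 12.

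Missingness would then depend on the outcome. The two affected results would be biased toward no deterioration, and more so in whichever arm did more harm, so a dose effect could be blunted. Section 1.1 names diabetic control as a particular interest of the study. Sections 4.1.5 and 4.1.9 intend the analysis to cover everyone who received a dose, and a paired Week 12 test and a Visit 7 count cannot do that for subjects who have left.

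**Working it through.** **1. The plan's own HbA1c sample size.** Section 4.1.5 gives 13 completers per group, a paired t-test and an effect size of 1. It states "Each comparison is made using a Type I error rate of 0.05" and "Each comparison is assessed using a Type II error rate of, at most, 0.2". Section 4.1.13 sets "two-sided tests of significance with no correction for multiplicity".

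Power = P(|T| > t(0.975, n−1)), with T noncentral t on n−1 degrees of freedom and noncentrality 1 × √n.
- n = 13: 91.1%
- n = 15: 94.9%
- smallest n reaching 80%: 10 (80.3%)

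So 13 is sufficient as stated. Enrolment also agrees: 13 / (1 − 2/15) = 15. The plan thus allows for losing 2 of 15 per arm. The problem is which subjects are lost, not how much power is lost.

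**2. Smallest rise in a subject removed on HbA1c.** Entry requires HbA1c below 10.0% (section 3.3.2), and the discontinuation criterion is above 12% (section 3.3.3). Taking the Week 0 value as below 10.0%, the rise exceeds 12 − 10 = 2.0 points. Removal on fasting glucose alone implies no minimum HbA1c rise.

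**3. Rise hidden when k such subjects are left out of an arm of 15.**

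Hidden rise = k × (rise in those removed − change in the rest) / 15

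| Rise in removed | Change in rest (assumed) | k = 1 | k = 2 |
|---|---|---|---|
| 2.0 (lower bound) | 0 | 0.13 | 0.27 |
| 2.0 (lower bound) | 0.4 | 0.11 | 0.21 |
| 4.0 (assumed) | 0 | 0.27 | 0.53 |
| 4.0 (assumed) | 0.4 | 0.24 | 0.48 |

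For scale, the 5% change that section 4.1.5 sizes for is 0.05 × 7 = 0.35 to 0.05 × 10 = 0.50 points at an assumed baseline of 7 to 10%.

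**4. Diabetes-control count.** Suppose the two losses allowed per arm are both glycaemic failures and only rated subjects are counted.
- 2/15 worsened (13%) becomes 0/13 (0%).
- 4/15 worsened (27%) becomes 2/13 (15%).

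**5. Would the paired test have found it anyway?** Let two of 15 rise by r and 13 not change.
- Mean = 2r/15 = 0.133r
- Variance = (2r² − 15 × (2r/15)²)/14 = 0.124r², so SD = 0.352r
- t = 0.133r / (0.352r/√15) = 1.47 on 14 degrees of freedom, two-sided p about 0.16
- Effect size = 0.133/0.352 = 0.38, against the planned 1

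The value of r cancels. In this pattern the paired test is not significant even with all 15 included, so what is distorted is the estimated mean change and the count, not a significance verdict.

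**The case against.** A reader might infer that every glycaemic failure is removed and that the trial's safety result as a whole loses its worst outcomes. The documents do not support that, for these reasons.

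- Section 3.3.3 says subjects may discontinue, and only after therapy adjustment has failed.
- Section 4.1.9 bases the safety assessment mainly on adverse events and out-of-range laboratory values in all dosed subjects, with shift tables to the most extreme post-baseline value. A study laboratory value that triggers removal stays in those summaries.
- Home glucose and dose adjustments also accrue until withdrawal.
- HbA1c from Weeks 4 and 8 can enter the repeated-measures analysis that sections 4.1.4 and 4.1.9 allow. A subject who first exceeds 12% at Week 12 is not lost at all.
- The schedule in Appendix 1 is not shown, so the termination assessment may include HbA1c or the rating. A detailed definition of the control endpoint may sit in an SAP.
- The 2-of-15 allowance is for general attrition, and assigning all of it to glycaemic failure is an assumption.

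All of this stands and limits the point to two secondary endpoints. It does not remove it. The analysis that keeps Weeks 4 and 8 is optional, while the paired test is fixed. Termination data are encouraged, not assured, and an off-schedule value does not enter a Week 0 to Week 12 pair without a rule. Section 4.1.12 is also not silent: it decides against any handling and gives a reason. Counting discontinuation as worsened control is one choice among several, so it should be shown beside the investigator's rating, not in place of it.

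**Conclusion.** The point holds for the paired Week 12 HbA1c test and the diabetes-control count. Under the plan as written, both can omit the subjects who deteriorated most and be biased toward no deterioration. The wider safety summaries and the optional repeated-measures HbA1c model do not share this fault.

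The size is illustrative. With no change in the rest of an arm of 15, the hidden rise is at least 0.13 points for one subject removed on HbA1c and at least 0.27 for two. If the rest rise by 0.4 points, the bounds fall to 0.11 and 0.21. The protocol gives no rate of glycaemic withdrawal and no baseline HbA1c mean or standard deviation. These are secondary endpoints in a small Phase II trial, so this is a correction worth making at low cost and not a flaw that undermines the study.

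**What to change.** Amend sections 4.1.12 and 4.1.4 and leave the stopping criteria unchanged.

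- **(a) HbA1c analysis.** Make the repeated-measures analysis the planned between-group analysis instead of an option. Use all post-baseline values (Weeks 4, 8, 12 and termination) in all treated subjects. Add a sensitivity analysis that carries forward the value at removal for subjects withdrawn for glycaemic failure.
- **(b) Termination assessment.** State that it includes HbA1c and the investigator's global rating of diabetes control.
- **(c) Diabetes-control endpoint.** Report it with all treated subjects as denominator, counting discontinuation under the glucose/HbA1c criterion as worsened, alongside the investigator-rated count. This does not depend on attendance at termination, because section 3.3.3 already requires the reason for discontinuation to be recorded.

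The cost is protocol wording, one HbA1c and one rating at an assessment the protocol already mentions, and slightly more analysis.

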### 4.1.13 Multiple Significance Testing

Unless otherwise specified, all p-values will be reported to four decimal places using two-sided tests of significance with no correction for multiplicity (multiple outcomes or multiple comparisons) having been employed. Statistical significance will be assessed at the conventional level of 0.05 in all cases unless otherwise stated, and thus any significant findings for parameters other than the primary endpoint must be interpreted accordingly.

### 4.1.14 Multicenter Considerations

It is anticipated that each center will have the same capacity to enroll patients. As such, patients will be recruited concurrently in time and in equal numbers at each of the centers. Once the

number of centers is finalized, target enrollment figures for each center may be amended to this section of the protocol.

The primary endpoint will be based on central laboratory assessments of the blood samples collected from oral glucose tolerance testing. Statistical methods that can separate the investigator (center) effect from the treatment and insulin use group effects will be used. It is not anticipated that there will be sufficient sample size to estimate possible interactions.

#### 4.1.15 Retrospective Power

No calculations of retrospective power are planned.

### 4.2 Data Management

#### 4.2.1 Database Design and Creation

An appropriate database will be designed and created within a suitable database management system. This database will be designed to store the data as recorded on the case record forms (CRFs) and will ensure a one-to-one mapping between the CRFs and the electronic copy as stored in the system.

